### Sample size and power

The study determined a sample size of 192 patients (96 per group) with a 5% dropout rate and a *P* value of 0.05 to achieve 90% power in detecting a 10% increase in time-weighted average SpO_2_/FiO_2_ during the initial post-extubation hour in the experiment strategy group, compared to the control group. The control group’s mean time-weighted average SpO_2_/FiO_2_ was estimated to be 294 with a standard deviation of 60, based on previous research [30], and the 10% difference between groups was determined from previous work showing that a decrease of 10% from baseline in PaO_2_/FiO_2_ was clinically meaningful in lung injury induced by ventilatory strategies [31–33]. A dropout rate of 5% was deemed acceptable for informed consent withdrawals post-enrollment.

### Statistical analysis

The data will be analyzed using R (version 4.3.3). The primary analysis will be carried out according to the intention-to-treat principle. The full analysis population (including all subjects who will be randomized and will be at least evaluated at baseline) will be used in the primary analysis. No interim analysis is planned. In case of missing data, the reason and mechanism for missing data will be explored. For missing data greater than 20%, multiple imputation may be considered as a sensitivity analysis to evaluate the treatment effect and associated standard error as appropriate.

Categorical variables are reported as number and percentage. Normally distributed variables are reported as mean and SD, non-normally distributed as median and IQR. Normal distribution of data will be assessed with the Kolmogorov–Smirnov test or the Shapiro–Wilk test. To compare continuous variables between experimental strategy and control strategy groups, Student’s *t*-test or Mann–Whitney *U* test will be used, as appropriate. Categorical variables will be compared using the Fisher exact test or likelihood ratio tests. The baseline and intraoperative parameters will be described per group (“experimental strategy” and “control strategy”) in accordance with the Consolidated Standards of Reporting Trials (CONSORT) guidelines.

The time-weighted average SpO_2_/FiO_2_ ratio will be compared as continuous variable. And treatment effects of primary outcome will also be analyzed according to the following subgroups: (1) age; (2) duration of cardiopulmonary bypass; (3) preoperative pathological chest image; (4) red cell transfusion during surgery. For secondary outcomes, the scores of pulmonary complications and severity of respiratory failure will be analyzed through Mann–Whitney *U* tests and multivariable ordinal logistic regression by estimating the common odds ratio for a shift in the direction of a better outcome on the modified scale. The proportion of other secondary endpoints (use of high-flow nasal cannula or non-invasive ventilation, use of new invasive mechanical ventilation, in-hospital mortality, adverse events) will be compared between the groups. Non-ventilatory support days and invasive mechanical ventilation days by postoperative day 7 will be compared between groups as continuous variables. Multiple comparison corrections will be performed for non-independent outcomes. The duration of ICU and hospital stay was compared using Kaplan–Meier curves and log-rank tests. The censoring was performed at postoperative day 28, and the time to event was the time from surgery end to ICU and hospital discharge. Patients who died before leaving the ICU or hospital were censored as nondischarged at day 28. A 2-sided *P* value < 0.05 was considered statistically significant.

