#### Baseline data

The following baseline data are collected after the patient’s inclusion: gender, age, height, weight, BMI, smoking status, history of COPD or asthma with chronic inhalation therapy, American Society of Anesthesiologists (ASA) score, Euroscore II, lower respiratory tract infection in the past 3 months, abnormal preoperative chest imaging, cardiovascular status (diabetes mellitus, arterial hypertension, dyslipidemia, liver disease, previous acute myocardial infarction, history of cardiac surgery, left ventricular ejection fraction, echocardiographic right ventricular distention defined by a right ventricle/left ventricle ratio > 1, brain natriuretic peptide level, cardiac troponin I level), and status of preoperative creatininemia > 3 mg/dL.

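### A normality check on the trial's own data decides the primary test, so the effect measure is not fixed; one prespecified, baseline-adjusted mean-difference model would fix it and use precision already available

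*Protocol article*

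**What the plan says.** Under Statistical analysis, the protocol article sets a general rule for continuous variables: "Normal distribution of data will be assessed with the Kolmogorov–Smirnov test or the Shapiro–Wilk test". Depending on that check, variables are summarised by mean and SD or by median and IQR, and the arms are compared by Student's t-test or Mann–Whitney U. The article does not say which normality test applies, at what threshold, or whether it is run per arm or on pooled data.

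The primary outcome gets only one further statement (apart from subgroups), that the "ratio will be compared as continuous variable". No model, covariate or effect measure is given.

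Under Sample size and power, the trial is planned around "detecting a 10% increase in time-weighted average SpO_2_/FiO_2_ during the initial post-extubation hour", from a control mean of 294 and SD of 60.

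Under Baseline data, the listed variables include "gender, age, height, weight, BMI, smoking status, history of COPD or asthma with chronic inhalation therapy", and also abnormal preoperative chest imaging. A multivariable model is named only for the two ordinal secondary outcomes: "multivariable ordinal logistic regression by estimating the common odds ratio for a shift in the direction of a better outcome".

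**The concern.** The sample size section commits the trial to a difference in means and justifies the 10% margin as clinically meaningful on that scale. The analysis section then lets the observed data decide whether that quantity is tested at all. If the check fails, the result becomes a rank comparison with medians, which cannot be read against the planned 29.4.

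This is not silence that an unseen analysis plan would fill. The article states a rule, and the rule depends on the data. Because it allows either of two normality tests of very different sensitivity, two analysts who both follow it could report different primary tests and effect measures from the same data.

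A smaller matter is that the primary comparison is unadjusted, although baseline variables are collected before allocation and the article already uses two of the recorded factors (age and preoperative chest imaging) to define subgroups of the primary outcome. Adjustment needs no new data.

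**Working it through.** **Inputs from the protocol article.** Control mean 294; SD 60; planned difference 10% of 294 = 29.4; standardised difference 29.4/60 = 0.49; two-sided alpha 0.05 ("A 2-sided *P* value < 0.05 was considered statistically significant"); sizing "with a 5% dropout rate and a *P* value of 0.05 to achieve 90% power"; 96 per group; 1:1 allocation.

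**Step 1: reproduce the plan's figure.** Normal approximation: n per arm = 2(1.960 + 1.282)² × (60/29.4)² = 87.5, so 88. The noncentral t gives 89 per arm. Allowing for 5% dropout, 89/0.95 = 93.7, so 94 per arm and 188 in total. The stated 192 agrees within about 2%. Conversely, 96 × 0.95 = 91.2, so about 91 evaluable per arm, with t-test power of 90.8%. The size is therefore consistent with a comparison of means.

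**Step 2: how open is the choice of test?** Simulation with 91 per arm, each normality test at 0.05 in each arm, and Mann–Whitney chosen if either arm rejects. The threshold, the per-arm use and the shapes of the distributions are assumptions; the article gives only the mean and SD. Plain Kolmogorov–Smirnov uses the estimated mean and SD without the Lilliefors correction.

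| Outcome shape | Shapiro–Wilk rejects | Plain Kolmogorov–Smirnov rejects |
|---|---|---|
| Normal | about 10% | 0% |
| Gamma, skewness 0.35 | about 36% | 0.2% |
| Gamma, skewness 0.5 | about 62% | 0.7% |
| Gamma, skewness 0.7 | about 89% | 3.6% |

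At skewness 0.5 the two permitted checks gave different answers in about 61% of trials. The Lilliefors version of Kolmogorov–Smirnov lies between them, rejecting in 8–57% of trials across these shapes.

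**Step 3: what does the selection cost?** In the same four shapes, the two-step rule using Shapiro–Wilk had type I error of 4.3–5.1%. At the planned effect its power was 90.3–92.3%, against 90.9–92.0% for the t-test alone, and the two tests disagreed on significance in 3–4% of trials. A separate, assumed scenario built the outcome from stepped FiO2 values. There Mann–Whitney was chosen in over 99% of trials, and two-step power was 86.4% against 90.6% for the t-test, with type I error still near 5%.

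**Step 4: what does adjustment add?** If the baseline variables explain a share R² of the outcome variance, the residual SD is 60√(1 − R²) and the standard error is that value × √(2/91). The article gives no R², so a range is assumed.

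| R² (assumed) | Residual SD | SE | Power at 91 per arm |
|---|---|---|---|
| 0 | 60.0 | 8.89 | 90.8% |
| 0.05 | 58.5 | 8.67 | 92.1% |
| 0.10 | 56.9 | 8.44 | 93.4% |
| 0.20 | 53.7 | 7.96 | 95.7% |

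The few degrees of freedom spent on covariates are ignored; with about 182 patients this is immaterial.

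**The case against.** The strongest reply is that the practical harm is small. An unadjusted comparison in a 1:1 randomized trial is valid, planned power is already 90.8%, and under mild skew the two-step rule loses almost no power and keeps its error rate. The Masking section also says that analysts work only after completion and without allocation information, which limits deliberate selection. The selection frequencies rest on assumed skewness and on choices the article does not state. All of this stands. It reduces the point to its proper size, but it does not supply a fixed effect measure: a blinded analyst must still let the data choose between a mean difference and a rank comparison.

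On adjustment, the reply is that the gain is not shown. That also stands in part. R² is assumed, the baseline list contains no preoperative SpO2/FiO2 or PaO2/FiO2, and the exclusions narrow the prognostic spread. At R² = 0.05 the gain is 1.3 percentage points of power.

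Three stronger readings are tempting, and the document does not support them:

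- A reader might infer that choosing the test after looking at the data inflates the false-positive rate. The simulations do not show this.
- A reader might infer that strong predictors of oxygenation are being ignored. No baseline oxygenation measure is listed, and the strength of the listed variables is unknown.
- A reader might infer that a linear model settles the whole estimand. It fixes the summary measure only. Patients who die or are never extubated have no value for this outcome, and the model does not say how to treat them.

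**Conclusion.** The point holds as a modest, cost-free improvement. The primary test and effect measure are left to a check on the trial's own data, in conflict with a sample size built on a mean difference of 29.4. At about 91 per arm the check is not needed for a valid comparison of means, and the two permitted versions of it can lead to different primary analyses.

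The size of the harm is limited to an unfixed effect measure and some unused precision. The only material power loss found, about 4 percentage points, depends on the assumed stepped-FiO2 distribution. The gain from adjustment depends wholly on the assumed R². The validity of the trial is not in question.

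**What to change.** For the primary outcome, drop the normality pre-test and state one analysis: a linear regression of time-weighted SpO2/FiO2 on arm, adjusted for named variables from the Baseline data list (for example age, BMI, smoking status, history of COPD or asthma, and abnormal preoperative chest imaging), with robust standard errors. Report the mean difference with its 95% confidence interval, and give Mann–Whitney as a sensitivity analysis. State how missing covariate values are handled.

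Do not adjust for gas exchange measured after intubation, which is recorded after randomization and may already reflect the first sighs. Do not adjust for type of surgery unless the planned procedure is captured before randomization; the article lists surgery type among the intraoperative variables. Add a separate statement on patients without a post-extubation value.

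The cost is a change of wording before unblinding. It needs no extra patients, visits or measurements.

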### Oversight and monitoring

No data monitoring committee (DMC) will be established in this trial as our investigator team could closely monitor participants’ safety and data integrity. Trial steering committee comprises two professors of intensive care medicine ([name] and [name]), a professor of cardiac surgery ([name]), a professor of anesthesiology (JS), and two independent statisticians. The trial steering committee convenes quarterly throughout the trial period to review trial conduct. This committee will validate the protocol, oversee the study, and have the authority to make decisions regarding its smooth running and publication strategy. And the Ethics Committee of Zhongda Hospital meets semi-annually or as needed to evaluate trial’s ethical conduct and the ethics committee has the authority to recommend modifications to the trial or its termination if significant concerns arise.

Any unforeseen medical events occurring in participants during the intervention period will be categorized as adverse events (AEs). Serious adverse events (SAEs) are defined as adverse events, including death, life-threatening situations, permanent or severe disability or loss of function, and the need for prolonged hospitalization, that occur following the trial treatment. All AEs will be meticulously recorded in the case report form (CRF), and SAEs will be promptly reported to the principal investigators. Upon identification of an AE, investigators will thoroughly assess the association between the intervention and the AE and determine whether to discontinue the intervention. All serious, unexpected, and study-related adverse events will be reported to the Ethics Committee of Zhongda Hospital within 15 calendar days. Patients who discontinue the intervention due to an AE will continue to be followed up. All patients in this study will be hospitalized in Zhongda Hospital. Accordingly, emergency care will be readily available at all times. The cost of treatment for all study-related adverse events will be covered by the trial initiator. The ancillary and post-trial care will be provided by a medical team, consist of cardiac surgeons, nurses, rehabilitation therapists, and intensivists, after the trial is completed.

Any modifications to the study protocol will necessitate synchronous protocol amendments, which will be promptly submitted for approval to the Ethics Committee/Institutional Review Board. These changes will only be implemented after approval by the ethical committee. Once approved, ClinicalTrials.gov will be promptly updated regarding any significant changes. If required, protocol training for the amendments will be provided by the study team.

## Discussion

The E-SIGHT trial is the first single-center, randomized controlled trial designed to evaluate the potential benefits of augmenting lung protective ventilation (LPV) with sigh breaths during the perioperative period in patients scheduled for cardiac surgery. This study aims to ascertain the feasibility and preliminary efficacy of this intervention in comparison to the conventional LPV approach. Should the feasibility be established, the E-SIGHT trial will lay the groundwork for a subsequent, more extensive clinical trial to definitively determine the efficacy of the sigh + LPV strategy in reducing postoperative pulmonary complications (PPCs). Furthermore, this research endeavors to introduce and assess a novel perioperative ventilation approach to mitigate the risk of postoperative hypoxemia and PPCs in patients undergoing cardiac surgery, ultimately enhancing their recovery in the postoperative period.

In the experimental arm, we have chosen a multimodal approach, from intubation to extubation, in order to reflect the prophylactic use nature of sighs, counteract with the risk of atelectasis which persists during the entire mechanical ventilation period. Sigh will not be administered during the opening of chest cavity giving the potential impact on the surgical procedure. The plateau change resulting from increasing PEEP producing a Pplat of 35 or 40 cmH_2_O was selected for two reasons. First, it produces an end-inspiratory lung volume that approximates total lung capacity in patients with normal chest wall and lung compliances, thereby facilitating secretion of surfactant. Second, a Pplat of 40 cmH_2_O has been utilized in numerous short-term studies of recruitment maneuvers in patients with ARDS without any evidence that it caused barotrauma or volutrauma [24]. In those patients with BMIs exceeding 35, the volume of the sigh breath will be determined on the basis of a Pplat of 40 cmH_2_O given the decrease in chest wall compliance that will be present. We did not choose an individualized PEEP titration protocol because of the absence of a validated reference titration protocol and because of the high risk of hemodynamic intolerance and barotrauma [34]. In both groups, PEEP level is selected according to low FiO_2_-PEEP table adopted from ARDS studies, its pragmatic design limited burden on daily activities and is moderate in comparison with previous studies in cardiac surgery [26]. During CPB, apnea was performed as no firm evidences of benefits of ventilation maintenance during CPB until nowadays [12, 35].

The primary outcome was the time-weighted average SpO_2_/FiO_2_ ratio during the initial post-extubation hour. Given the high sensitivity and specificity of SpO_2_/FiO_2_ in diagnosing acute lung injury without the need for repeated blood sampling [29], we consider it to be a suitable alternative to PaO_2_/FiO_2_. This is a very pragmatic endpoint, and previous performance in postoperative patients has proved good external validity [36]. To complementary for the primary endpoint, we evaluated long-term respiratory failure and postoperative pulmonary complications in the secondary outcomes, and the specific definitions allow for comparisons with previous studies [10, 12]. The need for non-invasive ventilation or high-flow nasal oxygen therapy has also been included in the secondary outcomes and standard procedures of postoperative ventilatory support were provided in the protocol. Finally, we will evaluate the invasive mechanical ventilation days during ICU stay, non-ventilatory support days, and endotracheal reintubation rate in postoperative day 7. Evaluating different outcomes with tight relationship with postoperative pulmonary function recovery will give a relatively comprehensive point of view on the impact of sigh approach.

One important limitation of the E-SIGHT trial is that double-blinding is not possible due to the nature of intervention. However, the outcome assessor will be blinded to the randomization arms, ensured the reliability of the study results. Second, in the absence of conclusive data on sigh “minimum effective dose,” we chose a rate of 5 s per 6 min because this frequency is considered to be close to the physiological state of a normal person [27]. Finally, we did not plan any biomolecular analysis to verify the impact of addition of sigh on lung protection for budget reasons; in any case, we will collect a huge amount of physiological data during the whole study period that will allow reconstruction on mechanistic effects underlying the clinical benefits.

In conclusion, E-SIGHT is a single-center randomized controlled trial to test the feasibility of long-term addition of sigh to lung protective ventilation. Its results could provide a ready-to-use treatment enhancing perioperative lung protection. Moreover, E-SIGHT will be the basis for planning a future larger trial investigating the use of sigh as a strategy to improve hard clinical outcomes in patients undergoing cardiac surgery through enhanced lung protection.

## Trial status

The E-SIGHT trial is currently recruiting patients. The protocol was approved by the Institutional Review Board on 22 February 2024. Current protocol version number was version 2, 10th Feb 2024. The first patient was enrolled on 25 February 2024. Recruitment is expected to be completed in October 2024.

## Data Availability

Any data collected in this study can be obtained from the corresponding author with a reasonable request.

## Abbreviations

CPB: Cardiopulmonary bypass
LPV: Lung protective ventilation
PEEP: Positive end-expiratory pressure
ARDS: Acute respiratory distress syndrome
PPCs: Postoperative pulmonary complications
ECMO: Extracorporeal membrane oxygenation
IABP: Intra-aortic balloon pump
BMI: Body mass index
VTs: Tidal volumes
SpO_2_: Pulse arterial oxygen saturation
FiO_2_: Fraction of inspiration oxygen
I:E: Inspiratory to expiratory ratio
Pplat: Plateau pressure
IPAP: Inspiratory positive airway pressure
EPAP: Expiratory positive airway pressure
VILI: Ventilator-induced lung injury
HFNO: High-flow nasal oxygen
CPAP: Continuous positive airway pressure
NIV: Non-invasive ventilation
SBT: Spontaneous breathing trial
OSAS: Obstructive sleep apnea syndrome
LVEF: Left ventricular ejection fraction
RASS: Richmond Agitation-Sedation Scale
GCS: Glasgow Coma Scale
CONSORT: Consolidated Standards of Reporting Trials
SPIRIT: Standard Protocol Items: Recommendation for Interventional Trials
